**4.3. Efficacy parameters**

4.3.1 The primary efficacy parameter is the number of patients in the two group that have achieved response to treatment or remission after 2, 9 or 29 weeks. Response is defined as a more than 50% reduction in HAM-D17 scores after inclusion into the study while remission is defined as a score of 7 or less on the HAM-D17.

4.3.2. Secondary effect parameter is the number of those patients in the two treatment groups who have experienced long-lasting response or remission after 9 weeks and after 29 weeks. Lasting response is defined as patients responding after 2 weeks of enrolment in the study and the response either lasting until week 9 (early lasting response) or until week 29 (episode response). Lasting remission is defined as being in remission after 2 weeks in the study and the remission either lasting until week 9 (early lasting remission) or until week 29 (episode remission). Response and remission are defined as mentioned under primary efficacy parameter. Patients who according to the protocol receive further sleep deprivations in week 4, 5, or 6 thus are cannot be defined as being in early, lasting remission. Response and emission are defined as mentioned under primary efficacy parameter. Patients who according to the protocol carry out additional sleep deprivation in weeks 4, 5 or 6 thus are defined not to be in early lasting remission.

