**11. STATISTICS**

To analyse the number of patients with response or remission at three defined points in time (weeks 2, 9 and 29), Chi2 distribution is used. To do this, the Last Observation Carried Forward (LOCF) is employed. The assessment of the longitudinal courses of response and remission (and sustained response and remission) uses survival analysis (Kaplan-Meier survival-analysis) including log-rank test to calculate p values (Stassen et al 1993). Furthermore, the Mixed Model Repeated Measures (MMRM) (Brown et al. 1999) will analyse readily available depression scores to determine the difference between the two groups. Thus, MMRM does not use LOCF. The association between cortisol and depression scores and the association between urine and saliva cortisol has been calculated by means of the Spearman correlation coefficient *rho*. The same statistical method will be used to test the association between the various degrees of depression and the effect of sleep deprivation. The idiographic method will be analysed by means of MMRM. Exercise will be analysed as the percentage of compliance to the predefined goal (30 minutes exercise daily). Moreover, the achieved amount of exercise (combined score of the Borg scale and the amount of performed exercise) will be graded into light/moderate/intensive in follow-up phase I. It will be compared with the degree of response and remission in week 29 and analysed by Chi2 distribution. The number of study subjects has been calculated on the basis of an expected depression score of 24 on the 17-item Hamilton Depression Scale at inclusion into the study for both groups. After 9 weeks of treatment a decrease to 10 in group A and to 13 in group B is expected. The expected standard deviation is 4. With a type-I error of 0.05 and 0.90 power, 39 patients are required for each group.

No interim analyses have been planned.

GCP guidelines permit that patients may be excluded from the data analysis after the end of the study, if eligibility violations have taken place and if this was not known during the project. This may refer patients who have fulfilled the inclusion criteria, but have not taken any of the study medication, or have taken other prescriptions without telling the investigator, and where these violations were not known until the end of the study. All other patients assessed at the time of inclusion in the study are included in the statistical analyses according to the intention-to-treat method.

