**12. DIMENSION**

According to the expected results of the study (see power calculation in the statistics section) and taking into account the possibility to analyse subgroups such as unipolar and bipolar patients, it is intended to include 100 patients into the study, 50 to each group. The patients are included consecutively and it will thus not be possible to foretell how many bipolars and how many unipolars will have been included at the end of the study.

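### The 0.90 power with 39 patients per group is for a week-9 mean HAM-D17 comparison, not for the primary chi-square tests of response and remission

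*Protocol*

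**What the plan says.** Section 4.3.1 of the protocol defines the primary outcome as a count: "The primary efficacy parameter is the number of patients in the two group that have achieved response to treatment or remission", assessed after 2, 9 or 29 weeks. Response is a fall of more than half in HAM-D17 from inclusion. Remission is a HAM-D17 of 7 or less. Section 11 analyses these counts at the three time points by chi-square with last observation carried forward.

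The same section sizes the trial on mean scores. It takes an "expected depression score of 24 on the 17-item Hamilton Depression Scale at inclusion into the study for both groups", then states: "After 9 weeks of treatment a decrease to 10 in group A and to 13 in group B is expected". It adds "The expected standard deviation is 4" and concludes "With a type-I error of 0.05 and 0.90 power, 39 patients are required for each group".

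Section 12 refers back to that calculation and, "taking into account the possibility to analyse subgroups such as unipolar and bipolar patients", sets the target: "it is intended to include 100 patients into the study, 50 to each group".

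**The concern.** The power calculation and the primary analysis concern different quantities. A comparison of means uses the whole score, whereas a comparison of proportions uses only the side of a cut-off on which each patient falls. Power computed for the first does not carry over to the second. The protocol gives no expected response or remission rates from which the power of the primary tests could be read, and it gives no expected values of any kind for weeks 2 and 29. Yet section 3 tests its main hypothesis at all three times and names faster onset as part of the main objective.

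The stake is interpretation. A reader who takes 0.90 as the power of the primary tests would treat a non-significant remission result as fairly strong evidence against a difference. Under the protocol's own expected effect, a separate week-9 remission test would miss significance about 30% of the time at 50 per group (1 − 0.70) and about 42% at 39 (1 − 0.58).

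**Working it through.** **Inputs from the protocol.** Section 11: baseline mean 24, week-9 means 10 (A) and 13 (B), SD 4, type-I error 0.05, power 0.90. Section 12: 50 per group planned. Section 4.3.1: the response and remission definitions.

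**Inputs assumed, because the protocol does not give them.** Two-sided testing (it reproduces the 39; one-sided gives 31), normal scores recorded as integers, and first a baseline of exactly 24 for everyone.

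**Step 1: reproduce the 39.** The normal approximation is n = 2σ²(z₀.₉₇₅ + z₀.₉₀)²/δ² = 2 × 16 × (1.960 + 1.282)²/9 = 37.4, so 38. With the noncentral t distribution, power is 0.897 at 38 and 0.905 at 39. The exact t-test answer is therefore 39. At 50 per group the same test has power 0.960. The stated figure is right for a difference in means.

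**Step 2: week-9 rates implied by the same means and SD.**
- Response: more than a 50% fall from 24 is a score of 11 or less. With cut-off 11.5, A is Φ((11.5 − 10)/4) = Φ(0.375) = 64.6% and B is Φ((11.5 − 13)/4) = Φ(−0.375) = 35.4%.
- Remission: with cut-off 7.5, A is Φ(−0.625) = 26.6% and B is Φ(−1.375) = 8.5%.

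**Step 3: power of the chi-square test.** Exact enumeration: sum Bin(x; n, p_A) × Bin(y; n, p_B) over all pairs (x, y) whose uncorrected Pearson statistic exceeds the 5% critical value of 3.84.

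| Week-9 comparison | 39 per group | 50 per group |
|---|---|---|
| Mean HAM-D17 (t-test) | 0.905 | 0.960 |
| Response | 0.76 | 0.86 |
| Remission | 0.58 | 0.70 |

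The usual large-sample formula gives slightly lower values: response 0.74 and 0.84, remission 0.56 and 0.67. By that formula, 0.90 power would need about 60 per group for response and 91 for remission, with baseline fixed at 24.

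**Step 4: let baseline vary.** Section 4.6.3 admits anyone scoring 13 or more, so baselines will not all be 24. A patient responds when Y − B/2 < 0, where Y is the week-9 score and B the baseline. This quantity has mean 10 − 12 = −2 in A and 13 − 12 = +1 in B. Its SD is s = √(16 + 0.25·SD_B² − 4·r·SD_B), where r is the correlation of baseline with week 9. For SD_B = 4, s is √20 = 4.47 at r = 0 and √8.8 = 2.97 at r = 0.7. The response powers below use integer scores and baselines of at least 13; each cell gives 39, then 50, per group.

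| Assumed r | SD_B = 3 | SD_B = 4 |
|---|---|---|
| 0 | 0.70, 0.81 | 0.66, 0.78 |
| 0.3 | 0.79, 0.88 | 0.77, 0.87 |
| 0.5 | 0.85, 0.93 | 0.86, 0.93 |
| 0.7 | 0.92, 0.97 | 0.94, 0.98 |

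Remission uses an absolute cut-off and stays at about 0.58 and 0.70 throughout.

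**Step 5: composite reading.** If response or remission is one combined outcome, almost every remitter starting near 24 is already a responder. In the same runs the power of the composite differs from that of response alone by no more than 0.002.

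**Scope.** All figures are for week 9 and for a single test at 0.05. For scale only, dividing 0.05 over six tests (two outcomes at three times) would give about 0.60 for response and 0.40 for remission at 50 per group.

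**The case against.** The best defence is that section 11 says openly what it calculated. It derives the number from expected depression scores and does not attach 0.90 to the chi-square test. The planned size is also 100 patients, not 78. Both points are fair: there is no arithmetic error, and figures at 39 per group should be read beside those at 50. But it is the only power statement in the protocol, and section 12 relies on it for the size of the whole trial. A reader will naturally take it to cover the primary outcome.

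A second point is that the chi-square powers need assumptions the protocol does not state: a distribution, a baseline spread and a baseline-to-week-9 correlation. This stands. A reader might infer that the response test falls short of 0.90. The documents do not establish that: at 50 per group a correlation of 0.5 already gives 0.93, and at 0.7 power exceeds 0.90 even at 39.

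Third, the primary parameter is worded "achieved response to treatment or remission after 2, 9 or 29 weeks", which can be read as one composite. On that reading the remission figures do not describe a primary comparison, and the power is that of response. This also stands. The remission shortfall is firm only if remission is tested separately.

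Finally, a reader might infer that the week-9 difference from the planned mixed model ought to become primary, since its power is assured. Neither part is supported. That model's power has not been computed here; the 0.905 and 0.960 are for a complete-data t-test. Moving the primary analysis to week 9 alone would also drop the week-2 and week-29 questions that section 3 asks.

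**Conclusion.** The point holds as a mismatch between the stated power and the primary analysis. The 0.90 with 39 per group is correct for a two-sided comparison of week-9 mean HAM-D17 and has not been shown for any primary test.

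- **Remission, if tested separately:** about 0.58 at 39 per group and 0.70 at 50, below 0.90 at both sizes whatever the baseline spread. This rests on normal integer scores with the protocol's means and SD.
- **Response, or the composite:** about 0.76 and 0.86 with baseline fixed at 24. The range is about 0.66 to 0.94 at 39 and 0.78 to 0.98 at 50 for an assumed baseline SD of 3 to 4 and correlation of 0 to 0.7. A shortfall is possible but not established.
- **Weeks 2 and 29:** no power can be derived for either outcome, because the protocol gives no expected values.

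**What to change.** In section 11, state that the 39 per group and 0.90 power refer to the two-sided comparison of mean HAM-D17 at week 9. Then add the week-9 power of the primary tests at 39 and at the planned 50 per group: response about 0.76 and 0.86, remission about 0.58 and 0.70. Give the assumptions (normal integer scores, baseline 24, each test at 0.05) and the response range under varying baseline. Say whether response or remission is one composite or two tests, since that decides whether the remission figures apply to a primary comparison. State that no power has been established for weeks 2 and 29.

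The cost is a few sentences and a less favourable stated power. No patients, visits or measurements are added. The sponsor may choose to make the week-9 mean difference primary, which would bring endpoint and calculation into line, but that changes the trial's main question and is not needed to correct the statement.

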4.1.1. Blinding procedures

It is not possible to blind the patient towards type of treatment (sleep deprivation or exercise). It is, however, possible to blind a permanent rater towards the treatment the patient has received. This can be done by having a rater who interviews and rates the patient each time throughout the whole study period by means of the Hamilton scale. The patients will be informed that they are not to disclose the type of treatment they receive to this permanent rater who assesses severity of depression according to Hamilton. There is no item in the Hamilton scale to reveal the type of treatment the patient receives, not even the sleep item, as all patients record their sleep in a sleep diary. The rater who conducts the interview will not meet the patient in the ward, as the regular visits are outside (before and after) the period of hospitalisation and will not be permitted to see patient records or CRFs. This rater will only receive the Hamilton rating sheet which does not contain information as to treatment group. All other procedures of the study will be performed by unblinded evaluators.

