4.1.3. Medication start phase**:** week 0 (7 days)

*Groups A and B*

After the patient has signed the informed consent form, an agreement concerning overnight stay is made with an in-patient ward in one of the county's psychiatric wards. When this has been decided, the patient can be included in the study and randomised to group A or B. All patients are switched from their present antidepressant treatment to duloxetine 60 mg daily in the morning. Patients who do not receive any current pharmacological treatment will also receive duloxetine 60 mg daily. Patient data are collected by means of questionnaires and forms as shown in flowchart 1 under inclusion visit. A deviation of +/- 2 days (window) of the duration of this phase due to a possible acute shortage of beds in the in-patient ward is acceptable.

Group B

At inclusion this group is also elucidated idiographically in regard to depression symptoms.

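### Section 11 lets eligible, randomised patients be dropped after the study for medication behaviour, yet calls the analysis of the rest intention-to-treat

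*Protocol*

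**What the plan says.** Section 11 (Statistics) contains the rule: "GCP guidelines permit that patients may be excluded from the data analysis after the end of the study, if eligibility violations have taken place". A proviso limits it to violations that did not come to light during the project. The text then describes whom it may concern, namely those said to "have fulfilled the inclusion criteria, but have not taken any of the study medication, or have taken other prescriptions without telling the investigator". Everyone else falls under the sentence that closes the section: "All other patients assessed at the time of inclusion in the study are included in the statistical analyses according to the intention-to-treat method".

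Three other sections bear on the rule:

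- **Section 4.1.3.** Once an overnight stay has been arranged, "When this has been decided, the patient can be included in the study and randomised to group A or B". The switch to duloxetine belongs to the week-0 phase that starts there.
- **Section 4.4.** Patients open their own allocation envelope on the day of inclusion.
- **Section 4.1.1.** The Hamilton rater is kept from records and case report forms, patients cannot be blinded, and "All other procedures of the study will be performed by unblinded evaluators".

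**The concern.** An intention-to-treat analysis keeps each randomised patient in the allocated group whatever happens afterwards. Section 11 uses the name but first removes a class of patients, at least partly for what they did after allocation. It calls the ground an eligibility violation, although one of its two examples (no study drug taken) cannot be an eligibility failure and the other need not be.

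Two features make this more than a matter of labelling. The rule is permissive, so like cases need not be treated alike. It also operates after the end of the study, when ratings have been collected, and it names no safeguard against knowledge of group or outcome. If the removed patients differ in prognosis between the groups, the comparison is no longer protected by randomisation. This would affect the response and remission counts at weeks 2, 9 and 29, which are the primary efficacy parameter (section 4.3.1).

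**Working it through.** The point concerns the analysis population, so most of the check is a comparison of texts. The arithmetic only shows how sensitive the comparison could be.

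**1. Are the two examples eligibility failures?**

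- *No study drug taken.* Randomisation takes place at inclusion (sections 4.1.3 and 4.4), and duloxetine is started in the phase that begins then. Never taking it is therefore post-randomisation behaviour. No criterion in 4.6.3 or 4.6.4 concerns taking the study drug.
- *Undisclosed prescriptions.* Section 4.6.4 excludes patients on antipsychotics and on drugs with a significant interaction with duloxetine. A patient could meet the three inclusion criteria in 4.6.3 and conceal such a drug at entry, which would be a true eligibility violation. The same words also cover a medicine taken weeks after randomisation. Section 11 does not distinguish the two.

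**2. Does any analysis keep all randomised patients?** The chi-square comparison with last observation carried forward, the survival analysis and the mixed model are all described in section 11. The only population stated there is the remainder after exclusions. No analysis is described that puts the excluded patients back.

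**3. Who knows what when exclusions are made?** Allocation is known to patients and to all evaluators except the Hamilton rater (4.1.1). Data are entered consecutively and analysed immediately after the last patient finishes (section 13). Section 11 does not require the decision to be blind to group or outcome.

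**4. The plan's own sample size.** Inputs from section 11 are week-9 means of 10 and 13, SD 4, type-I error 0.05 and power 0.90. With a two-sided test, n = 2 × [4 × (1.960 + 1.282) / 3]² = 37.4, so 38 by the normal approximation. The noncentral t gives power 0.897 at 38 and 0.905 at 39, so the stated 39 per group is reproduced. At the planned 50 per group (section 12) power is 0.96. Keeping all randomised patients requires no change in sample size.

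**5. Illustration with no true difference.** Assumptions, not protocol figures: the same true response rate of 40%, 50% or 60% in both groups, 50 per group, k non-responders removed from one group only, and an uncorrected Pearson chi-square. The apparent difference is p × 50/(50 − k) − p. For p = 0.5 and k = 5 this is 0.5 × 50/45 − 0.5 = 0.056. Type I error is by exact enumeration.

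| Removed from one group | Apparent difference, percentage points | Two-sided type I error |
|---|---|---|
| 0 | 0 | 0.052-0.057 |
| 2 | 1.7-2.5 | 0.058-0.063 |
| 5 | 4.4-6.7 | 0.074-0.116 |

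**6. Illustration near the significance threshold.** Assumed counts are 31/50 responders in A and 22/50 in B. Chi-square = 100 × (31 × 28 − 19 × 22)² / (50 × 50 × 53 × 47) = 3.25, p = 0.071.

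| Removal | Comparison | p |
|---|---|---|
| 2 non-responders from A | 31/48 v 22/50 | 0.041 |
| 3 non-responders from A | 31/47 v 22/50 | 0.030 |
| 2 non-responders from B | 31/50 v 22/48 | 0.108 |
| 2 non-responders from each | 31/48 v 22/48 | 0.065 |
| 3 non-responders from each | 31/47 v 22/47 | 0.061 |
| 1 responder and 1 non-responder from A | 30/48 v 22/50 | 0.067 |

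Of these, only the removals confined to non-responders in A cross 0.05. With a continuity correction, two such removals give 0.066 and three give 0.049.

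**The case against.** The case on the other side has real substance.

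- **The trial is not open-label.** A reader might infer that it is, since patients know their treatment. Section 4.1 calls it single-blind, and 4.1.1 and 4.4 keep the Hamilton rater from the allocation. The HAM-D17 ratings behind response and remission are therefore protected. That protection covers the ratings and does not extend to the decision to exclude.
- **Not every undisclosed prescription follows randomisation.** A reader might infer that both examples are post-randomisation by nature. The exclusion criteria in 4.6.4 show otherwise for a concealed drug. The defect is that the two situations are merged.
- **The reach is narrow.** The rule covers only violations unknown during the project, so patients who openly refuse or withdraw are outside it. Ward staff give the medication during hospitalisation and study drug is logged at each visit (4.5.5). Psychiatric drugs are also checked at each visit (section 5). Total non-intake that stays hidden to the end should be rare. Both groups receive duloxetine, so dislike of the allocation is not an obvious motive for secretly avoiding it. This limits the likely size but does not make the rule neutral.
- **Leaving out patients who took no drug is a common modified intention-to-treat convention.** This is the milder half. Even so, the protocol does not call its population modified, and duloxetine is common to both groups. Not taking it does not mean that the randomised intervention was missed.
- **A statistical analysis plan may regulate who decides and when.** It may, and a reader should not infer that exclusions will in fact be chosen with the results in view, because section 11 does not say so. But the protocol itself fixes the ground for exclusion and the label, and a plan that follows it inherits the conflict.

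**Conclusion.** The concern holds in this form: section 11 permits discretionary exclusion, after the study, of randomised patients who met the inclusion criteria, and then applies the name intention-to-treat to the remainder. The rule and its label conflict. Because allocation is widely known and no blind decision is required, the rule can bias the primary comparison.

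The size is unknown. The documents give no expected number of exclusions and no reason to expect them in one group more than the other. The type I error range of 0.074 to 0.116 rests on five one-sided removals of non-responders and on assumed response rates. A reader might take the move from p = 0.071 to 0.041 as a forecast. It is a constructed worst case on assumed counts, and balanced or mixed removals do not produce it. What the figures do support is that, with 50 per group, a handful of one-sided exclusions can matter.

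Whether GCP guidelines permit such exclusions cannot be judged from the protocol, and the conclusion does not depend on it.

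**What to change.** Rewrite the last paragraph of section 11 along these lines:

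1. The primary analysis includes every randomised patient with an inclusion HAM-D17, in the group allocated. The plan already carries the last observation forward for response and remission, so this adds no new method.
2. A patient may be excluded only if an inclusion or exclusion criterion was objectively unmet before randomisation. The decision is made before database lock by someone blind to group and outcome, and is recorded with its reason. A concealed drug listed in 4.6.4 and in use before randomisation falls here.
3. Patients who took no study drug, or who used undisclosed medicines after randomisation, stay in the primary analysis and are left out only in a per-protocol sensitivity analysis.

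The cost is wording only. The sample size does not change, and the estimated effect may be slightly smaller.
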